## Exploratory Objectives

- - - 1. To examine whether HSCT caregivers participating in a stress reduction intervention demonstrate improvement in certain individual factors (self-efficacy, burden, and mindfulness), psychosocial factors (stress, anxiety, depression, loneliness, positive affect and well-being), behaviors (health behaviors) and symptoms (sleep, fatigue, depression, and cognitive impairment) compared with HSCT caregivers in the control group.
      2. To examine whether HSCT caregivers participating in a stress reduction intervention demonstrate improvement in physiological markers of stress (serum cortisol) and clinical (blood pressure, waist circumference, body weight) and biomarkers of inflammation and cardiometabolic disease (lipids profiles, fasting blood glucose, insulin, IL6, TNF-alpha, hs-CRP) compared with HSCT caregivers in the control group.
      3. To examine whether the amount of yoga practiced by HSCT caregivers in the intervention group contributes to improvement in individual factors, psychosocial factors, behaviors, symptoms, as well as physiological markers of stress and clinical and biomarkers of inflammation and cardiometabolic disease.
      4. To characterize subjects with a significant change in perceived stress or other study outcomes (ie: sleep disturbance, depression, anxiety, loneliness) following the intervention, to generate possible hypotheses for future research.

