All participants will receive usual care education (UCE), which includes transplant specific information for the recipient and the caregiver, as well as caregiver resources. After study enrollment, caregiver subjects will be randomized to either the control group or the intervention group. A permuted block randomization with allocation ratio of 1:1 will be performed by the study statistician. All participants will meet 1:1 with a study investigator to review the UCE materials. Participants in the intervention group will also receive an audio recording of a 20 minute yoga-based stress reduction intervention, as well as instructions on how to complete the intervention; they will be asked to practice the twenty minute audio file daily for the six weeks of the intervention. The six-week length of the intervention, as well as the 20 minute time of the audio file, was selected based upon the length of similar interventions in other caregiver populations, with interventions ranging between four to ten weeks [^37^](#_ENREF_37)^,^[^43^](#_ENREF_43). All study visits will be scheduled around the HSCT recipient’s schedule and visits to minimize burden for the caregiver. The initial visit for all participants will occur prior to the patient’s initial discharge from the hospital and within 7 days of the HSCT infusion (Day 0+7). Subjects in the intervention group will receive a brief phone call at weeks two and four (+/- 7 days) to assess progress and to record practice. All subjects will participate in an exit interview at week six (+/- 7 days). Study questionnaires will be administered to all subjects at baseline and again at week six (+/- 7 days). Completion will take approximately 20 minutes through a web-based system. If the electronic system is unavailable, a hard copy of the questionnaires will be available for completion. Caregivers in either group who complete baseline assessments but are no longer able to return to the clinical center for their week 6 study visit will be given the option to complete the week 6 questionnaires electronically.

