## 6.2 Statistical Analyses

Initial data analysis will consist of examining the frequency distributions for all variables at both time points and computing descriptive statistics appropriate for the level of measurement (e.g., mean and standard deviation for interval level data, median for ordinal level data). Linear mixed repeated measures analysis will be used to analyze the effect of intervention on the primary outcome of perceived stress. The primary analysis will be based on intention-to-treat, which will include all of the randomized subjects. The last observation carried forward method will be used to impute missing data. However, if an enrolled subject comes off study before being randomized, they will be replaced. A sensitivity analysis will be performed for all subjects with complete data at both time points.

The effect of intervention on the exploratory outcome variables as described in the objective section will also be examined by linear mixed models. Any demographic covariates will be included in the model if significantly associated with the outcome and significantly different between the groups. To examine the effect of practice variation on the study outcomes, practice time will be included in the linear mixed models for the intervention group only. Aikake information criterion and the Bayesian information criterion will be used to select best fitting models. Appropriate data transformation technique will be used if necessary.

If no significant differences are found between groups, the responders with clinically meaningful changes in the intervention group will then be characterized. No minimal clinically important differences have been established for our primary outcome, the PSS, therefore, we will use the method proposed by Norman, Sloan, and Wyrwich (2003) of accepting changes in .5 standard deviation as clinically important [^87^](#_ENREF_87). Responders and non-responders will be compared on the basis of their demographic characteristics such as gender and age.

In addition to the primary analysis outlined above, exploratory hypotheses generating analyses will be performed to examine the relationships among caregiver factors. Methods of correlation and regression analysis will be used to evaluate the relationships between outcomes of interest and study variables. All inferential tests will be conducted at the .05 level of significance.

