Appendix D: Telephone Script and Exit Interview

**Interviewer Instruction**: Intervention Group (Q1-7 for telephone follow-up at weeks 2 and 4, as well at exit interview at week 6); Control Group (Q8 at exit interview at week 6 ONLY)

[Thank the subjects for their participation in the study. Remind the subject of the study design and the plan to have a total of three calls, 2, 4 and 6 weeks]. Explain the purpose of the call: To evaluate frequency of practice –based on their diary (not memory) – and to identify barriers to daily practice. Confirm that they have their diary with them during the call.]

1. *How many times in the last two weeks have you practiced the complete audio (from beginning to end)?*
2. *On the days when you did not practice the entire audio CD, how many times did you start the audio but were unable to finish? [if >1, as them to ‘list’ the reasons for not completing]*
3. *On the days when you were not able to practice, please tell me what prevented you from practicing*
4. *Did you have any problems or issues when you were practicing?*
5. *In general, on a scale of 1 to 10, with one being not motivated and 10 being very motivated, how motivated were you to practice in the last 2 weeks?*
6. *In general, on a scale of 1 to 10, with one being not very confident and 10 being very confident, how confident are you that you will continue to practice?*
7. *Is there anything you would like to tell us about your experiences with your practice, or do you have any questions of us?*

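### The practice-time model in 6.2 does not isolate improvement, and carried-forward values can mimic a dose-response (exploratory objective 3 only)

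*Protocol*

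**What the plan says.** Exploratory objective 3 in the Protocol is "To examine whether the amount of yoga practiced by HSCT caregivers in the intervention group contributes to improvement in individual factors" and in the other outcome domains listed there. The only analysis sentence for it is in 6.2: "practice time will be included in the linear mixed models for the intervention group only". That sentence does not say whether practice enters as a main effect, as an interaction with time, or as a covariate that is zero at baseline.

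On missing data, 6.2 says "The last observation carried forward method will be used to impute missing data". The sentence follows the description of the intention-to-treat primary analysis but is not restricted to it. Section 6.2 also says "A sensitivity analysis will be performed for all subjects with complete data at both time points", without saying which models this covers.

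Outcomes are measured twice, at baseline and at week 6 (section 3.0 and Figure 3). All practice comes after baseline. A daily practice diary is kept (Figure 3) and collected (Appendix B). Section 10.1 reports 10% attrition in the earlier caregiver study, and section 10.3.1 takes a caregiver off study on the day the transplant recipient dies.

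**The concern.** How much a caregiver practises is chosen by the caregiver, not randomised. Caregivers under more strain may practise less, or more. A practice term that does not vary over time, placed in a two-visit mixed model, is tested against each caregiver's average of the two visits. Half of that average was recorded before anyone had practised. If less stressed caregivers practise more, the term will suggest that practice lowers stress even when it does nothing.

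A term aimed at change meets a different problem. With two visits, LOCF means that baseline is carried forward, so an early leaver's change is exactly zero. The same person's practice total is cut short by leaving. If stress falls on average among those who stay, low practice goes with no improvement because of the imputation alone.

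At stake is the reading of the dose-response result. It would naturally be taken as support for the intervention, and the exploratory work is meant to shape later research.

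**Working it through.** **Inputs from the Protocol.** 39 per arm, correlation 0.80 between visits, effect size 0.6, two-sided 0.05 and 80% power (6.1); 10% attrition (10.1).

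**Assumptions not in the Protocol.** Baseline stress-practice correlation r of -0.2 to -0.5; mean practice 25 of 42 days with SD 10; a leaver's practice cut at a uniformly random fraction; mean within-arm fall in stress of 0 to 0.6 SD; attrition above 10%. The 0.6 in 6.1 is a difference between groups, so using it as a within-arm change is also an assumption.

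**Plan's own figure.** No figure is given for the practice analysis. The arm size reproduces: 2 × (1.960 + 0.842)² / 0.6² = 43.6, times (1 + 0.80)/2 = 0.9, gives 39.24, stated as 39. That factor is the variance of the mean of two visits. It does not show how practice will enter the model.

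**Plain practice term, no true effect, no dropout.** The test equals a regression of the two-visit mean on practice. The implied correlation is r × √((1 + 0.80)/2).
- r = -0.3: -0.3 × √0.9 = -0.285. Fisher z: atanh(0.285) × √36 = 1.756, so the rejection rate is Φ(1.756 - 1.960) = 0.42.
- Simulation (6,000 runs per case) gives 0.21, 0.42 and 0.88 at r = -0.2, -0.3 and -0.5.

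**Change-type term (practice by time), no true effect, LOCF, r = 0.** Simulated rejection rates:

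| Attrition | Mean change 0 | 0.3 SD | 0.6 SD |
|---|---|---|---|
| 10% | 0.038 | 0.053 | 0.100 |
| 20% | 0.032 | 0.076 | 0.197 |

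With complete cases and a 0.6 SD change, the rates return to 0.052 (10%) and 0.048 (20%). With LOCF at 10% but practice unrelated to leaving, the rate is 0.051. The artefact therefore needs both shortened practice among leavers and a non-zero mean change.

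**Do the two mechanisms add up?** No. Under the plain term, LOCF at 10% attrition and a 0.6 SD change gives only 0.060 when r = 0.

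**Does practice by time solve the first problem?** Not fully. Regression to the mean gives an implied correlation with change of -r × √((1 - 0.80)/2). At r = -0.3 this is 0.3 × √0.1 = 0.095, and 0.095 × 6 = 0.57 gives about 9% rejection. At r = -0.5 it is about 16%. Simulation gives 0.090 and 0.165. The sign is opposite to that under the plain term.

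**Observed week-6 outcome adjusted for baseline.** Under the same null scenarios the rejection rate is about 5%.

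**The case against.** The strongest reply is that 6.2 never says main effect. Because nobody has practised at baseline, an analyst could code practice as zero at baseline and as the total at week 6. That coding, with visit in the model, rejects in 5.8% and 6.1% of null trials at r = -0.3 and -0.5. A term's exact form is often left to a statistical analysis plan, and one may exist. This stands in part: the 42% is conditional on the plain reading and on a correlation that the Protocol does not give. It does not dispose of the point. Recoding practice leaves the carried-forward values in place, and 6.2 hands model choice to information criteria, which judge fit and not whether the term answers objective 3.

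It is also fair that the LOCF sentence may be meant for the primary analysis only, that a complete-data analysis is planned, and that section 3.0 lets caregivers who cannot return complete week 6 electronically. If the complete-data analysis covers the practice model, it removes the LOCF artefact, provided that leaving is unrelated to outcome. It does not address the selection of practice.

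A reader might also infer that the contact schedule creates false findings. The Protocol plans a "brief phone call at weeks two and four (+/- 7 days) to assess progress and to record practice", so consecutive contacts can be up to 35 - 7 = 28 days apart, while the scripted question looks back two weeks. The documents do not support that inference. Appendix D has answers taken from the diary and not from memory, section 3.2 treats the contacts as verification, and nothing says that practice time is the sum of the call answers. Random recording error would weaken a true association (power 0.79 falling to 0.45 in one simulated case) and would leave the false-positive rate at 5% to 6%.

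**Conclusion.** The point holds in a limited form. As written, the practice analysis can give a misleading dose-response by one of two routes, depending on the form of the term. A plain term picks up pre-existing differences in stress: 21% to 88% false positives over assumed correlations of -0.2 to -0.5, and about 42% at -0.3. A change-type term combined with LOCF gives about 5% to 10% at the Protocol's 10% attrition, for a mean change of 0.3 to 0.6 SD, and about 20% at 20% attrition and 0.6 SD. With no mean change there is no inflation.

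A reader might conclude that the plan is bound to produce false dose-response findings, or that the two routes compound. Neither follows: each route depends on assumptions outside the Protocol, and they apply to different models. Severity is minor. Only exploratory objective 3 is affected, and the randomised comparison is not.

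**What to change.** In 6.2, replace the practice-time sentence with one on these lines: within the intervention group, the observed week-6 value of each outcome will be regressed on total practice between baseline and week 6, taken from the daily diary, adjusting for the baseline value of that outcome; carried-forward values will not be used, and the result will be reported as a non-randomised association.

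Both parts are needed. Baseline adjustment deals with the pre-existing link between stress and practice, and using observed values removes the artefact from early leavers. A practice-by-time term is not an adequate substitute, because it keeps about 9% to 16% false positives at correlations of -0.3 to -0.5.

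The cost is one sentence and no new data, since the diary is already collected. The analysis loses caregivers without a week-6 value, about 4 of 39 at 10% attrition (0.10 × 39 = 3.9). Confounding by factors other than the baseline outcome remains, which is why the result should be called an association.

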# 6.0 BIOSTATISTICAL CONSIDERATIONS

## 6.1 Sample size

The study is a randomized controlled trial with two groups: stress reduction and control (standard education) using permuted block randomization with allocation ratio of 1:1. The primary objective of this study is to investigate whether HSCT caregivers in the stress reduction group demonstrate improved levels of stress compared to those in the control group. Power analysis was performed based on the primary objective only. We used a two-sided hypothesis that the PSS level will differ between the intervention group and the control group. We assume an exchangeable correlation structure of PSS. Based on an effect size of 0.6 [^40^](#_ENREF_40)^,^[^85^](#_ENREF_85) and correlation of 0.80 between two time points from our biomarker study, with 80% power and type I error of 0.05, in order to detect a difference between the stress reduction group and the control group, we will need 39 participants in each group and a total sample size of 78 [^86^](#_ENREF_86).

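### The responder analysis is planned only in the intervention arm after a null result, with no control benchmark, so it cannot separate response from change that would occur anyway

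*Protocol*

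**What the plan says.** Section 6.2 of the Protocol sets out the responder step as follows: "If no significant differences are found between groups, the responders with clinically meaningful changes in the intervention group will then be characterized". Because no minimal important difference exists for the PSS, the section adopts a published convention "of accepting changes in .5 standard deviation as clinically important". It does not say which SD is meant (baseline or change score), nor that the change must be an improvement. It continues: "Responders and non-responders will be compared on the basis of their demographic characteristics such as gender and age". It closes with a general rule: "All inferential tests will be conducted at the .05 level of significance".

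The matching aim is exploratory objective 4: "To characterize subjects with a significant change in perceived stress or other study outcomes", with sleep disturbance, depression, anxiety and loneliness given as examples, "following the intervention, to generate possible hypotheses for future research". The objective carries no condition on the primary result and names no arm.

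Section 3.0 has both arms complete the same questionnaires at baseline and at week 6, so change scores will exist for controls as well.

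**The concern.** A change of half an SD within one arm mixes several things: any effect of the intervention, measurement fluctuation, regression to the mean, and whatever happens to caregivers' stress over the six weeks after transplant. The randomized control arm is there to separate the first from the rest. The responder step leaves it out, and does so in the one situation where the randomized comparison has not shown an effect.

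At stake is the use that objective 4 has in view, namely hypotheses for later research. If the share of controls who change as much is unknown, a characteristic that differs between responders and non-responders cannot be read as a predictor of benefit. It may only mark caregivers whose scores would have moved anyway.

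A second issue is scope. Objective 4 is broader than the analysis written to serve it, both in when it applies and in which outcomes it covers.

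**Working it through.** **Inputs.** The correlation between the two time points is 0.80 (section 6.1: "correlation of 0.80 between two time points from our biomarker study"). Section 6.1 also gives 39 per arm, an effect size of 0.6, two-sided alpha 0.05 and 80% power. The threshold is 0.5 SD (section 6.2). Attrition in the earlier caregiver study was 10% (section 10.1). Assumptions of this check: normal scores, equal variance at both visits, baseline SD as the unit.

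**The plan's own figure.** The Protocol gives no number for the responder analysis. Its sample size is reproduced to within rounding when the compared quantity is the mean of the two time points, with variance factor (1 + 0.80)/2 = 0.90:

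n per arm = 2 × 0.90 × (1.960 + 0.842)² / 0.6² = 39.24, with power 79.75% at 39.

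So 39 and 0.80 are consistent inputs. Nothing below depends on that derivation.

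**Chance rate of a half-SD improvement.** With no effect and no mean change, the SD of change in baseline-SD units is √(2(1 − ρ)), and

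P(improve by ≥ 0.5 SD) = Φ(−0.5 / √(2(1 − ρ))).

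At ρ = 0.80, SD of change = √0.40 = 0.632 and P = Φ(−0.79) = 0.215. Then 39 × 0.215 = 8.4 caregivers. The same share is expected in the control arm, so the expected excess is zero.

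| Correlation | SD of change | P(improve ≥ 0.5 SD) | Of 39 |
|---|---|---|---|
| 0.50 (assumed) | 1.000 | 30.9% | 12.0 |
| 0.70 (assumed) | 0.775 | 25.9% | 10.1 |
| 0.80 (Protocol) | 0.632 | 21.5% | 8.4 |
| 0.90 (assumed) | 0.447 | 13.2% | 5.1 |

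**Sensitivity to what section 6.2 leaves open, at ρ = 0.80.**

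- If the SD meant is that of the change scores: Φ(−0.5) = 30.9%, or 12.0 of 39.
- If change in either direction counts: 2 × 21.46% = 42.9%, or 16.7 of 39.
- If 10% drop out and their baseline is carried forward, they show zero change and count as non-responders: 8.4 × 0.9 = about 7.5.
- If both arms share a time trend (assumed; the Protocol gives none), P = Φ(−(0.5 − m)/0.632). Improvement of m = 0.2 or 0.3 SD gives 31.8% or 37.6% (12.4 or 14.7 of 39). Worsening by the same amounts gives 13.4% or 10.3% (5.2 or 4.0 of 39).

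**Conditioning on the trigger.** I simulated 20,000 trials per setting with 39 per arm and ρ = 0.80, used a t test on change in place of the primary test, and kept only non-significant trials.

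| True effect (SD) | Intervention rate | Control rate | Control / intervention |
|---|---|---|---|
| 0 | 21.5% | 21.4% | 1.00 |
| 0.1 | 25.7% | 22.0% | 0.86 |
| 0.2 | 29.9% | 23.2% | 0.78 |
| 0.3 | 34.0% | 24.5% | 0.72 |

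With no effect, the central 5–95% range was 5 to 13 labelled responders, and every non-significant trial had at least one. With a modest true effect, the intervention arm shows a real excess, but most labelled responders are matched by the control background. The excess can be seen only because the control rate is set beside it.

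**Scope.** Section 6.2 plans the responder step for a non-significant between-group result and sets out the half-SD threshold for the PSS. Objective 4 has no such trigger and includes other outcomes. If the primary result is significant, section 6.2 names no responder analysis. For the other outcomes it sets out no threshold.

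**The case against.** The strongest reply is that this is openly exploratory. Objective 4 seeks hypotheses, the trial is powered on the primary objective alone, and no confirmatory claim rests on the responder step. That stands, and it limits the weight of the point. It does not rescue the method, because the analysis cannot serve even its hypothesis-generating purpose if it cannot tell benefit from background change.

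Three stronger readings are tempting, and the Protocol does not support them.

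- A reader might infer that the analysis would simply label chance as response to yoga. That is exact only if the true effect is zero, which a non-significant test does not establish. At a true effect of 0.3 SD, the simulated rates among non-significant trials were 34.0% against 24.5%, so some labelled responders would be genuine.
- A reader might infer that section 6.2 contradicts objective 4 and abandons it if the trial is positive. The objective states a broad aim without a method, and section 6.2 describes one conditional analysis. The last paragraph of 6.2 also plans, without condition, correlation and regression between outcomes and study variables. That is not a responder analysis and states no comparison of arms, but it does relate outcomes to caregiver characteristics. The mismatch is one of scope.
- A reader might infer that any predictors found would be markers of high baseline stress and would misdirect the next study. Under the model above, change does correlate with baseline at −√((1 − 0.80)/2) = −0.32. But the planned comparison is on demographics, and the Protocol does not show that these track baseline stress.

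It can also be said that replacing the step with interaction models is a matter of preference and would have low power with 78 caregivers. That is fair, and the fix does not depend on it.

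**Conclusion.** The point holds as a should-fix on an exploratory analysis. As written, the responder step has no control-arm benchmark, so it cannot separate response to the intervention from fluctuation, regression to the mean or a shared time trend. On the protocol's correlation of 0.80, assuming no effect, no mean change and the baseline SD as the unit, about 21% of an arm (about 8 of 39) would qualify by chance. The 31% figure (about 12 of 39) rests on an assumed correlation of 0.50. If a modest effect exists, some labelled responders would be real, but the analysis could not show which characteristics predict benefit rather than change that would occur anyway. The trigger and the PSS-only threshold are narrower than objective 4 and should be reconciled with it. The primary test, its type I error and the sample size are not affected.

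**What to change.** Amend section 6.2 as follows.

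- Whatever the primary result, report the proportion of caregivers improving by at least 0.5 baseline SD on the PSS in both arms, with the between-arm difference and its 95% CI. Name the SD and the direction.
- If responders and non-responders are still compared within the intervention arm, label the result as a description of change, not of response to yoga.
- Align the section with objective 4: either drop the null-result trigger and give a rule for the other outcomes, or narrow the objective.
- Optionally, add arm-by-characteristic interactions using all caregivers, marked as low-powered and hypothesis-generating.

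The cost is wording and a small amount of analysis. Both arms already supply the data at baseline and week 6, and no further visits or participants are needed.
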